**(2)**

where r is the ratio of cases to controls (1 in this instance given the equal numbers in the two groups), P_1_ is the proportion of exposed individuals in the cases, P_2_ is the proportion of exposed individuals in the controls, P* is the effect size (P_1_ – P_2_), Z_β_ at 80% power is 0.84, and Z_α/2_ is 1.96 for a .05 significance level at the 95% CI.

According to Caccamo et al [6], the prevalence of vitamin D deficiency among women with GH (P_1_) and that among pregnant women without hypertension (P_2_) is 21% and 11%, respectively. Therefore, P* is determined to be 0.1 (0.21–0.11). Applying equation 2, the sample size is calculated as:

n = (1 + 1) × (0.1) × (1 – 0.1) × (0.84 + 1.96)^2^/1 × (0.1)^2^

n = 141

Considering dropout or missing samples, 10% attrition is added to the calculated sample size. Hence, our minimum number of participants in each group (cases and controls) was determined to be 150.

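### The Phase 2 sample-size formula puts the difference (0.10) where the mean exposure proportion (0.16) belongs, so 150 per group gives about 66% power for 21% vs 11%, not 80%

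*Protocol article*

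**What the plan says.** The section on sample size for the case-control study (Phase 2) gives a formula for comparing two proportions with these inputs:

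- Significance: Z_α/2 "is 1.96 for a .05 significance level at the 95% CI".
- Power: Z_β "at 80% power is 0.84".
- Case-to-control ratio r: "1 in this instance given the equal numbers in the two groups".
- Prevalence of vitamin D deficiency in women with gestational hypertension (P1) and in pregnant women without hypertension (P2): "is 21% and 11%, respectively".

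P* is defined as the effect size, P1 − P2: "Therefore, P* is determined to be 0.1", with the difference 0.21 − 0.11 given as its source. The substitution is "n = (1 + 1) × (0.1) × (1 – 0.1) × (0.84 + 1.96)^2^/1 × (0.1)^2", with result 141. The section then says that 10% is added for attrition and concludes: "Hence, our minimum number of participants in each group (cases and controls) was determined to be 150". The abstract and the total sample size section repeat 150 per group as the Phase 2 target.

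**The concern.** In equation 2 the squared difference (P1 − P2)² is in the denominator. The factor P*(1 − P*) in the numerator has a different job: it is the variance of a binary exposure, evaluated at the average proportion across the two groups. Using the difference there has no statistical meaning. It would make the supposed variance shrink towards zero as the two groups became more alike.

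The value used is also impossible as an average. It gives 0.10 × 0.90 = 0.090, which is below the variance in controls (0.11 × 0.89 = 0.098) and in cases (0.21 × 0.79 = 0.166). The variance is understated, so the sample size is too small.

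This is the only power statement for Phase 2. If it is wrong, the planned comparison has a clearly higher chance of missing the targeted difference than the protocol tells its readers, and the strengths section presents the sample size as an advantage. A non-significant Phase 2 result would then carry less information than the stated 80% implies.

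**Working it through.** **Inputs**, all from the Phase 2 sample-size section: Z_α/2 = 1.96, Z_β = 0.84, so (Z_β + Z_α/2)² = 2.8² = 7.84; r = 1; P1 = 0.21; P2 = 0.11; attrition 10%.

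**1. The plan's own figure.** n = [(r + 1)/r] × P*(1 − P*) × (Z_β + Z_α/2)² / (P1 − P2)².

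With P* = 0.10: 2 × 0.10 × 0.90 × 7.84 / 0.01 = 141.1. The stated 141 is reproduced, so it does come from using the difference as P*.

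**2. The same equation with the mean proportion.** P* = (0.21 + 0.11)/2 = 0.16.

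2 × 0.16 × 0.84 × 7.84 / 0.01 = 210.7, so **211 per group**.

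Other two-sided versions agree:

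| Version | n per group |
|---|---|
| Pooled two-proportion | 210 |
| Pooled, continuity correction | 230 |
| Unpooled variance | 207 |
| Arcsine | 206 |

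A one-sided 0.05 test would still need 166.

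**3. Power at the planned size.** Inverting equation 2, power = Φ( √[n × (P1 − P2)² / (2 × 0.16 × 0.84)] − 1.96 ).

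For n = 150: √(150 × 0.01 / 0.2688) = 2.362; 2.362 − 1.96 = 0.402; Φ(0.402) = 65.6%.

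The pooled two-proportion z-test, two-sided 0.05, for 21% vs 11% gives:

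| Analysed per group | Power |
|---|---|
| 135 (150 less 10%) | 61.2% |
| 141 | 63.1% |
| 150 | 65.8% |
| 211 | 80.2% |

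At 150 per group, the unpooled version gives 66.4% and the arcsine version 66.6%. A one-sided 0.05 test gives 76.6%. None of these reaches 80%.

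**4. Attrition.** 141 × 1.1 = 155.1, and 141/0.9 = 156.7. The figure of 150 adds only 150/141 − 1 = 6.4%. Losing 10% of 150 leaves 135, below the plan's own 141. Phase 1 applies the same allowance correctly: 376 × 1.1 = 413.6, reported as 414. Applied to 211, the allowance gives 211 × 1.1 = 232.1 or 211/0.9 = 234.4, that is, about 232 to 235 per group.

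**5. What 150 per group can detect.** With 11% exposure in controls and all 150 analysed, 80% power requires about 23.1% in cases. The odds ratio is then (0.231/0.769)/(0.11/0.89) = 2.43. The planned 21% vs 11% corresponds to (0.21/0.79)/(0.11/0.89) = 2.15.

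**The case against.** The algebra is not in dispute. The strongest objection is that 21% vs 11% is not the comparison that Phase 2 makes. These are prevalences of vitamin D deficiency. Phase 2 recruits only women already classified as deficient and compares VDR genotypes between those with and without hypertensive disorders. Deficiency cannot differ between two groups that are all deficient, so neither 80% nor 66% is the power for the genotype comparison.

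The detectable odds ratio of about 2.4 is equally tied to 11% exposure in controls. The document gives no genotype frequencies. Over an assumed range of control frequencies, an odds ratio of 2.4 with 150 per group has power of about 50% at a frequency of 5%, 79% at 11%, 92% at 20% and 97% at 40%.

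This point stands, but as a separate defect. It does not rescue the 80% claim, which fails on the inputs the protocol itself chose. It does mean that any corrected figure must be stated as conditional on those inputs.

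Three smaller points:

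- **Attainability.** Even 150 per group may be out of reach. In December 2023 there were 22 cases and 50 controls, with recruitment due to end in March 2024. At the observed 63% deficiency, 414 women would yield about 0.63 × 414 = 261 deficient women of all ethnicities, fewer than the 300 Malay women needed. This makes 61% to 66% optimistic if anything.
- **Method.** The planned analysis is logistic regression with several covariates, so two-proportion power is an approximation. The protocol's own calculation uses the same approximation.
- **Reading of a null result.** The document does not say that a null result will be taken as evidence of no association. That consequence is a risk to readers, not something the plan commits to.

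**Conclusion.** The concern holds. The difference was used in place of the mean proportion, and the attrition allowance was then under-applied. On the protocol's own inputs the requirement is 211 per group before attrition, not 141. The planned 150 per group gives about 66% power if everyone is analysed and about 61% after 10% loss. The chance of missing the planned difference is therefore about 34% to 39% instead of 20%.

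These figures assume two-sided alpha 0.05, equal groups, an unadjusted comparison of two proportions, and that 21% and 11% are the relevant exposure proportions. The last assumption is doubtful for the genotype comparison, whose power cannot be derived from anything the document gives.

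**What to change.** In the Phase 2 sample-size section:

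1. Define P* as (P1 + P2)/2 = 0.16 and show the corrected result, 211 per group.
2. Correct the attrition step: 141 plus 10% is not 150, and 10% on 211 gives about 232 to 235.
3. Withdraw the statement that 150 per group is the minimum for 80% power.
4. If enrolment stays at 150 per group, state what it gives: about 66% power for 21% vs 11% with no loss, about 61% with 10% loss, or 80% power for an odds ratio of about 2.4 at 11% control exposure with no loss.
5. State beside these figures that they are conditional on the deficiency prevalences used as inputs and do not describe power for the genotype comparison.

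The cost is protocol wording only, with no added recruitment. The price is a less favourable power statement.

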**(1)**

where n is the minimum sample size, Z is the level of significance at the 95% CI (1.96), p is the prevalence rate, q = 1 − p, and d is the tolerable margin of error (5%).

According to Woon et al [26], the prevalence of vitamin D deficiency among Malaysian pregnant women is 42.6%. Applying equation 1, the sample size is calculated as follows:

n = (1.96)^2^ × 0.426 × (1 – 0.426)/(0.05)^2^

n **=** (3.8416 × 0.426 × 0.574)/0.0025 = 376

Therefore, the minimum sample size required for the cross-sectional study after addition of a 10% attrition rate is approximately 414 Malaysian pregnant women.

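### Phase 2 adds 10% attrition to 141 per group but states a minimum of 150, which allows for only about 6% loss

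*Protocol article*

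**What the plan says.** The section on sample size determination for the case-control study (phase 2) works equation 2 with r = 1, P* = 0.1, a difference of 0.1, 80% power (0.84) and two-sided 5% significance (1.96), and prints n = 141. On the ratio it states that "r is the ratio of cases to controls (1 in this instance given the equal numbers in the two groups". It then says "Considering dropout or missing samples, 10% attrition is added to the calculated sample size" and draws the conclusion that "our minimum number of participants in each group (cases and controls) was determined to be 150". The Abstract (Methods) and the Total Sample Size section repeat 150 per group without further explanation.

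The phase 1 section uses the same percentage. It obtains "3.8416 × 0.426 × 0.574)/0.0025 = 376" and reports that the size "after addition of a 10% attrition rate is approximately 414 Malaysian pregnant women".

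**The concern.** The phase 2 text prints the starting figure, the operation and the result, and the result is not what the operation produces. The same 10% raises the phase 1 figure by 10% and the phase 2 figure by about 6%.

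The figure is offered as the minimum that still leaves enough women after dropout or missing samples. If losses reach the planned level, phase 2 falls below the number that the plan itself says it needs, and the stated 80% power is missed even on the plan's own terms. A reader who cites 150 as already covering 10% loss would be misled.

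**Working it through.** **Inputs.** From the phase 2 section: r = 1, P1 = 0.21, P2 = 0.11, P* = 0.1 (as the plan uses it), Z values 0.84 and 1.96, 10% attrition, final size 150 per group. From the phase 1 section: p = 0.426, d = 0.05, Z = 1.96, 10% attrition, final size 414.

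**Step 1: the plan's figure before attrition.**
n = (r + 1) × P* × (1 − P*) × (0.84 + 1.96)² / [r × (P1 − P2)²]
= 2 × 0.1 × 0.9 × 2.8² / 0.01 = 141.12.
This reproduces the printed 141.

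**Step 2: the attrition step.**
- Adding 10%: 141 × 1.1 = 155.1, so 156 per group.
- Allowing for 10% loss: 141 / 0.9 = 156.7, so 157 per group.
- Stated: 150 per group.

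Neither usual reading of a 10% allowance gives 150.

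**Step 3: what 150 does allow for.**
- Increase over 141: 150 / 141 − 1 = 6.4%.
- Loss tolerated before falling below 141: 1 − 141 / 150 = 6.0%.
- Left after 10% loss: 150 × 0.9 = 135, which is 6 below 141.

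**Step 4: power under the plan's own formula.** Rearranging equation 2 for r = 1, power = Φ(√[n × (P1 − P2)² / (2 × P* × (1 − P*))] − 1.96), with 2 × 0.1 × 0.9 = 0.18.

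| Evaluable per group | Calculation | Power |
|---|---|---|
| 150 (no loss) | Φ(√(150 × 0.01 / 0.18) − 1.96) | 82.3% |
| 141 (6% loss) | Φ(√(141 × 0.01 / 0.18) − 1.96) | 79.9% |
| 135 (10% loss) | Φ(√(135 × 0.01 / 0.18) − 1.96) | 78.2% |

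**Step 5: phase 1 for comparison.** n = 1.96² × 0.426 × 0.574 / 0.05² = 375.7, so 376. Adding 10% gives 376 × 1.1 = 413.6, so 414. The phase 1 figure follows from its stated operation. The same operation in phase 2 gives 156.

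**The case against.** The strongest reply is that the consequence is small. Up to about 6% loss, 150 per group still leaves 141, and at the full 10% the shortfall in power is under two percentage points. That stands, and it limits the weight of the point. It does not rescue the figure: nothing in the article explains 150, and rounding 155 down to 150 is not compatible with calling it a minimum.

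Three stronger readings are tempting, and the document does not support them.

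- **Phase 1 misapplies attrition too.** A reader might note that 10% loss from 414 leaves 372.6, below 376, and that 376 / 0.9 = 418. But phase 1 says that 10% is added and calls the result approximate, and 376 × 1.1 is 413.6. Choosing between multiplying by 1.1 and dividing by 0.9 is a matter of convention. The gap is about 1%, and the margin of error at 372.6 is 5.02% against 5.00%.
- **The minimum should be 142, since 141.12 rounds up.** This is true in principle and trivial. It does not alter the conclusion.
- **Power is really about 61%.** That figure appears at 135 per group if the average proportion, (0.21 + 0.11) / 2 = 0.16, replaces P* = 0.1. Almost all of the drop comes from that replacement: on the same basis, power at 141 per group is only about 63%. It belongs to the separate question of how P* is defined and cannot be charged to the attrition step.

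**Conclusion.** The point holds for phase 2 only. The stated minimum of 150 per group does not include the 10% allowance that the text says was added. It is 6 or 7 per group below the figure that the allowance implies (156 or 157), covers about 6% loss, and at 10% loss leaves 135 per group with about 78% power instead of 80%.

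These power figures take the plan's formula and inputs as given, including P* = 0.1, and assume that the full 10% is lost in each group. They show that the section is inconsistent with itself. They do not establish the true power of phase 2. The definition of P* as the difference between P1 and P2 is a separate and larger problem: with the average proportion 0.16, the same formula gives 2 × 0.16 × 0.84 × 2.8² / 0.01 = 210.7, so 211 per group before attrition. A reader should therefore not infer that moving from 150 to 156 or 157 would make phase 2 adequately sized.

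**What to change.** In the phase 2 sample size section, do one of the following.

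1. Keep 150 per group, state that it allows for about 6% attrition, and report the power expected at 10% loss (about 78% under the plan's own inputs). This is a change of wording only and needs no further recruitment. The stated position becomes slightly less favourable.
2. Keep the 10% allowance and correct the minimum to 156 per group (adding 10%, as in phase 1) or 157 (dividing by 0.9). The total becomes 312 or 314 instead of 300, and the Abstract and the Total Sample Size section must be changed to match.

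State which inflation rule is used, and apply it to any phase 2 size recalculated once P* is corrected. The phase 1 figure of 414 can stay as it is.

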### Ethical Considerations

The research protocol has been approved by the Ethics Committee for Research Involving Human Subjects of the Universiti Putra Malaysia (reference number JKEUPM-2021-915). The study will be conducted in accordance with the standards of human experimentation in the Declaration of Helsinki and Malaysian Good Clinical Practice Guideline. This study protocol was also registered with ClinicalTrials.gov (NCT05659173). All eligible participants will be given a patient information sheet consisting of information about the study. Those who agree will be asked to sign a written consent form (available in both the Malay and English languages). Participation is voluntary and participants have the right to withdraw at any time without giving a reason. Any amendment to the protocol or documents will be submitted for review to the ethics committee. To preserve the privacy of the participants, any personal details will be removed from publications. Only anonymized and deidentified information will be made available in future manuscripts related to this work. All data of the study will be kept in a password-protected database on a password-protected desktop computer at the host organization and will only be accessible by the named researchers. As this is an observational cross-sectional and case-control study, there will be no compensation given to the participants given that the study is determined to be of low risk.

### Data Analysis Plan

Data obtained from the study will be analyzed using SPSS version 27.0 (IBM Corp). Data entered will be checked for missing or suspicious values. These will subsequently be verified with the participants or omitted as missing values. Descriptive analysis will be used to summarize the sociodemographic data, anthropometric data, clinical data, vitamin D dietary intake, sun exposure, and physical activity. The prevalence of vitamin D deficiency will be expressed in frequency and percentage. The association with sociodemographic data will be analyzed using the *χ*^2^ test, independent *t* test, and ANOVA where applicable.

We will report the comparative prevalence of *BsmI*, *ApaI, TaqI,* and *FokI*
*VDR* genotypes among Malay pregnant women with vitamin D deficiency with and without HDP. Similarly, the distributions of *VDR* genotype and allele frequencies according to vitamin D deficiency among Malay pregnant women will be reported as a descriptive analysis. Any mutations found in the *BsmI*, *ApaI, TaqI,* and *FokI* VDR gene fragments among Malay pregnant women with HDP will also be described. The associations of vitamin D status, associated risk factors, and VDR genetic variants with HDP will be determined using multivariate logistic regression analysis. The level of significance will be considered at a threshold of *P*≤.05 at the 95% CI.

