## Methods

### Objectives

The objectives of this prospective study are to (1) determine the prevalence of vitamin D deficiency and associated risk factors among Malaysian pregnant women; (2) determine the frequencies of *BsmI*, *ApaI, TaqI,* and *FokI* genotypes among Malay pregnant women with vitamin D deficiency and HDP; (3) understand and associate the distributions of *VDR* genotype and allele frequencies in relation to vitamin D deficiency among Malay pregnant women; and (4) identify mutations in the *BsmI*, *ApaI, TaqI,* and *FokI* VDR gene fragments among Malay pregnant women with HDP.

This study is divided into two phases. Phase 1 is a cross-sectional study involving Malaysian pregnant women to achieve objective 1, whereas phase 2 is a case-control study among Malay pregnant women to achieve objectives 2, 3, and 4.

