### Cross-Sectional Study (Phase 1)

#### Participants and Data

To achieve objective 1, Malaysian pregnant women, at any stage of gestation, with a singleton viable pregnancy at the time of recruitment and who are literate in the English or Malay language will be recruited. Women with a multiple pregnancy and on vitamin D supplementation are excluded. The gestation stage will be determined from the first day of the last menstrual cycle or based on measurement of the fetal crown-rump length determined on an ultrasound scan. Pregnant women taking vitamin D supplements or those who have been diagnosed with chronic diseases that are known to affect vitamin D levels, such as autoimmune disease and cancer, are excluded from the study.

Clinical, sociodemographic, dietary intake, and anthropometric (height, weight, and BMI) data will be collected using a pro forma. The prepregnancy BMI (kg/m^2^) will be calculated by dividing the weight (kg) by the square of the height (m^2^). Weight will be determined from prepregnancy body weight recall or obtained from the woman’s antenatal booking record along with the measured height. Participants will then be interviewed by a single trained interviewer to answer a validated questionnaire to determine their risk factors associated with vitamin D deficiency.

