## Discussion

### Projected Significance

The study will provide information on the current prevalence and modifiable risk factors of vitamin D deficiency. The prospective associations of vitamin D deficiency with the study variables will be of immense benefit to physicians and public health experts in formulating policies related to vitamin D supplementation. The outcome will greatly advance our current understanding of vitamin D deficiency in Malaysia and at mechanistic level could be adopted by other low- and middle-income countries to tackle the widespread problem of vitamin D deficiency.

Additionally, this study holds promise for determining the influence of unchangeable genetic components that may impact vitamin D deficiency and its correlation with HDP. This will constitute a significant new development in the field. Determining the association of the genetic variants will enable gaining a further understanding of the roles of the nonmodifiable components contributing to the risk of vitamin D deficiency that lead to the development of HDP.

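### For risk factors under Objective 1, the plan states only unadjusted tests on sociodemographic data, so the promised modifiable factors have no stated test and no adjusted estimate

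*Protocol article*

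**What the plan says.** In the protocol article, Objectives, the first aim is to "determine the prevalence of vitamin D deficiency and associated risk factors among Malaysian pregnant women", and "Phase 1 is a cross-sectional study involving Malaysian pregnant women to achieve objective 1". Under Cross-Sectional Study (Phase 1), Participants and Data, women are interviewed to "answer a validated questionnaire to determine their risk factors associated with vitamin D deficiency".

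The Data Analysis Plan then assigns methods by type of data:

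- "Descriptive analysis will be used to summarize the sociodemographic data, anthropometric data, clinical data, vitamin D dietary intake, sun exposure, and physical activity".
- After a sentence on reporting prevalence, the association sentence opens "The association with sociodemographic data will be analyzed using the" and lists the chi-square test, independent t test and ANOVA.
- "The associations of vitamin D status, associated risk factors, and VDR genetic variants with HDP will be determined using multivariate logistic regression analysis".

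The Discussion (Projected Significance) states: "The study will provide information on the current prevalence and modifiable risk factors of vitamin D deficiency". Strengths and Limitations adds that assessing these factors will help in understanding cause and effect. The Conclusion says that the study will determine both modifiable and nonmodifiable factors for deficiency.

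**The concern.** Phase 1 serves only Objective 1, and its questionnaire is adapted, translated, piloted and validated to measure risk factors for deficiency. Yet the factors that a woman or a health service could change (diet, sun exposure, activity, weight) are the ones for which the plan states only a summary. The one group of variables with a stated test is sociodemographic, and those tests take one variable at a time.

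Adjustment matters in this population. Phase 1 takes "Malaysian pregnant women, at any stage of gestation, with a singleton viable pregnancy at the time of recruitment", and it is not restricted to one ethnic group. Ethnicity, gestation, BMI, sun exposure and diet may well be correlated, and a one-variable contrast cannot separate them. At stake is the risk-factor half of Objective 1, and with it the Discussion's claim to inform supplementation policy. The prevalence estimate is not affected.

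**Working it through.** **1. Which stated analysis could answer the risk-factor question?**

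- *Descriptive summary* covers diet, sun exposure, physical activity, anthropometric and clinical data. It gives no measure of association with deficiency.
- *Chi-square, t test, ANOVA* are stated for sociodemographic data. They are unadjusted.
- *Multivariable logistic regression* has HDP as its outcome, and vitamin D status is a predictor. It estimates associations with HDP and not with deficiency.
- *Phase 2 data* cannot fill the gap. Case-Control Study (Phase 2), Participants and Data, recruits women already classified as deficient, so deficiency does not vary there.

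No stated analysis gives a test of the modifiable factors against deficiency, or an adjusted estimate for any factor.

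**2. The plan's own sample size.** Inputs from Sample Size Calculation for the Cross-Sectional Study: Z = 1.96, p = 0.426, d = 0.05, attrition 10%.

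- n = Z² × p × (1 − p) / d² = 3.8416 × 0.426 × 0.574 / 0.0025 = 375.7, rounded up to 376.
- 376 × 1.10 = 413.6, rounded up to 414.

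Both figures reproduce. The size rests on the precision of the prevalence alone and on no risk-factor comparison.

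**3. Can that sample carry an adjusted model?** Prevalence is 42.6% (planning value) or 63% (Results, preliminary). Smaller class = N × min(p, 1 − p). The allowances of 10 or 20 women per parameter are assumptions and are not in the article.

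| N | Deficient | Smaller class | At 10 per parameter | At 20 per parameter |
|---|---|---|---|---|
| 414 | 42.6% | 414 × 0.426 = 176 | 17 | 8 |
| 414 | 63% | 414 × 0.37 = 153 | 15 | 7 |
| 376 | 42.6% | 376 × 0.426 = 160 | 16 | 8 |
| 376 | 63% | 376 × 0.37 = 139 | 13 | 6 |

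As an example, assume three ethnic groups (2 parameters) and one linear term each for gestational age, BMI, sun exposure, diet and physical activity (5). That is 7 parameters, and the worst row gives 139 / 7 = 19.9 women per parameter.

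**4. How much could confounding matter?** The article gives no associations among the factors, so this is illustration only. Assume an exposure with no true effect on deficiency, a binary confounder present in 50%, and exposure in 40% of women without the confounder. The confounder has the same odds ratio with exposure and with deficiency.

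Worked case, odds ratio 2 and 42.6% deficient:

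- Exposure with the confounder: odds 0.667 × 2 = 1.333, so 0.571. Overall exposure: (0.40 + 0.571) / 2 = 0.486.
- Deficiency is 0.342 without and 0.510 with the confounder, which averages 0.426.
- Deficiency in the exposed: (0.5 × 0.40 × 0.342 + 0.5 × 0.571 × 0.510) / 0.486 = 0.441.
- Deficiency in the unexposed: (0.5 × 0.60 × 0.342 + 0.5 × 0.429 × 0.510) / 0.514 = 0.412.
- Crude odds ratio: (0.441 / 0.559) / (0.412 / 0.588) = about 1.13.

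For confounder odds ratios of 1.5, 2 and 3, the crude odds ratios are about 1.04, 1.13 and 1.33. At N = 414, an unadjusted test then rejects in the direction of the bias about 4%, 8–9% and 29–30% of the time, against 2.5% nominal in that tail. The results at 63% are almost the same.

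**The case against.** The strongest reply is that this is a short plan in a journal article. It does not say that diet or sun exposure will not be tested, and a fuller analysis plan may name a model. Sociodemographic may also be loose shorthand, since Projected Significance speaks of associations between deficiency and the study variables in general. Moreover, neither Objective 1 nor the Discussion promises independent or adjusted associations, and an unadjusted association can meet a descriptive aim.

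Part of this stands. A reader might infer that diet and sun exposure will go untested. The article supports only that it states no test for them. A reader might also infer that the Phase 1 results will be confounded. The article gives no correlations from which to show that, and the illustration runs from a negligible bias to a material one. Nor can the plan be faulted for breaking a promise of independent associations, because it makes none.

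The reply does not remove the point. The article names sun exposure, diet and physical activity and assigns them a method, and it names a multivariable model for HDP, so the choice of model was within its scope. That choice does not match Objective 1. Statements about cause and effect and about determining modifiable factors also go beyond what unadjusted contrasts on sociodemographic data can carry.

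**Conclusion.** The point holds as a mismatch between objective, stated method and intended conclusion. Followed as written, the Data Analysis Plan gives the risk-factor half of Objective 1 unadjusted tests on sociodemographic data, no stated test of the modifiable factors, and no model with deficiency as outcome. The associations are open to confounding whose size the documents do not let one estimate; the crude odds ratios of 1.04 to 1.33 come from assumptions and are not a forecast.

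The planned sample is large enough for the remedy: about 13 to 17 parameters at 10 per parameter, or 6 to 8 at 20. This assumes 376 to 414 women with complete data, and that the 42.6% and 63% figures apply at the article's own deficiency cut-off of 30 nmol/L. The article does not say which cut-off lies behind either figure; another one would shift the class sizes.

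**What to change.** Add to the Data Analysis Plan, for Phase 1, a prespecified multivariable logistic regression of deficiency (below 30 nmol/L versus higher) on ethnicity, gestational age at sampling, prepregnancy BMI, sun exposure, dietary vitamin D and physical activity. Report adjusted odds ratios with 95% confidence intervals and keep the chi-square, t test and ANOVA results as descriptive. Include clothing only if the questionnaire records it; the article mentions it only as background. A linear model of log 25(OH)D could be added but is optional.

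If no such model is wanted, limit the statements in Projected Significance, Strengths and Limitations, and Conclusion to unadjusted associations, and say which variables were tested.

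The cost is one extra analysis of Phase 1 data, with no extra participants. Results reports only a preliminary prevalence, with other analyses pending, so at the time of the article the model could still be fixed before any risk-factor result was seen.
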